#### CMR acquisition of first-pass perfusion and late gadolinium enhancement images

2.4.5

Myocardial first-pass perfusion images will be acquired using a saturation recovery turbo spoiled gradient-echo sequence at every heartbeat over 70 beats in three image SAX planes (basal, mid-ventricular, and apical). At start, two proton density-weighted images will be acquired at all three levels for correcting surface-coil SI inhomogeneity. In patients with a heart rate exceeding 80 beats per minute, the three slices will be acquired in 2 heartbeats/concatenations. Stress arterial input function (AIF) and perfusion images will be acquired after at least 3 min of constant intravenous infusion of adenosine at a dose of 140 μg/kg/min (or higher if necessary, as described above). AIF images will be acquired during intravenous administration of a pre-bolus of GBCA (DOTAREM®, Guerbet, Villepinte, France; 0.5 mmol/mL) at a dose of 0.0075 mmol/kg. Perfusion images will be acquired using a main bolus of GBCA (Dotarem, Guerbet, Villepinte, France; 0.5 mmol/mL) at a dose of 0.075 mmol/kg [31]. Patients will be asked to hold their breath as long as possible and breathe slowly thereafter. Rest AIF and perfusion images will be acquired using identical scanning parameters, pre-bolus and bolus doses, and slice location at least 10 min after adenosine administration.

Late gadolinium enhancement (LGE) images will be acquired 12–15 min after rest perfusion using a two-dimensional segmented inversion recovery gradient-echo pulse sequence.

#### CMR image post-processing

2.4.6

All CMR images will be anonymized before the analysis. CMR post-processing and analysis will be conducted by readers who are blinded to the patients’ clinical data, including ICA results, and other CMR-derived results. Images will be analyzed using certified software equipped with a pixel-wise QP module and a prototype of dedicated software for the analysis of dynamic changes in myocardial oxygenation in OS-CMR images.

The QP module automatically corrects in-plane respiratory motion of the heart and surface coil-induced signal inhomogeneities (using proton density images), as described previously [67], [68]. Next, the system detects the AIF and myocardial ROIs to derive time-SI curves and identify key time points during first-pass contrast enhancement [69]. The software deconvolves the AIF and myocardial time-SI curves on a pixel-by-pixel basis to generate MBF estimates and obtain fully quantitative MBF maps [25]. Myocardial segmentation is done automatically [70]. Inappropriate automatic delineation of myocardial ROIs will be corrected by the operator. Quantitative analysis will include measurement of stress and rest MBF (mL/g/min), myocardial perfusion reserve (MPR; calculated as a ratio of MBF at stress over rest), relative MBF stress and rest (rMBF; calculated as a ratio of MBF to MBF of a remote segment showing the second highest value), and relative MPR (rMPR; calculated as a ratio of MPR to MPR of a remote segment showing the second highest value). These parameters will be calculated for all automatically determined myocardial segments according to the American Heart Association (AHA) 17-segment model, excluding apex [71]. In addition, the automated 32-segment model based on the 17-segment AHA model, excluding the apex and with epi- and endocardial subdivisions, will be applied.

Qualitative assessment of stress first-pass perfusion CMR and LGE images will be done by two independent level 3 CMR-certified experts under the supervision of a third level 3 expert with the highest experience in stress-perfusion CMR imaging. Scan quality will be graded as uninterpretable, poor, average, or good. First-pass stress-perfusion and LGE images will be visually analyzed according to the AHA 17-segment model, excluding the apex. Each myocardial segment will be assessed for the amount of stress-perfusion defect and LGE and scored according to a 5-point score: 0: 0%, 1: 1–25%, 2: 26–50%; 3: 51–75%; and 4: >75%. Presence and extent of ischemia and LGE will be scored by two (primary and secondary) independent level 3 CMR-certified experts. In case of discordance between the readers, the primary and secondary graders will evaluate the scan together. If discordance cannot be resolved, a third and final expert reader will evaluate the scan, and this assessment will be used for the analyses.

T1 maps will undergo quality control before post-processing, using the raw MOLLI images. Endocardial and epicardial contours will be placed manually, and partial volume effects from the blood and extra-myocardial tissues will be carefully avoided. Regional rest and stress T1 values will be measured according to the AHA 17-segment model, excluding apex. ∆T1 will be calculated as (stress T1 − rest T1)/rest T1 × 100%.

Before the post-processing of OS-CMR, the image quality will be assessed by a reader experienced in OS assessment. The OS analysis will be performed in end-systole to allow for the greatest contouring area. Epicardial and endocardial contours will be drawn by the software and (if necessary) corrected by the operator with careful attention to avoid inclusion of intracavitary blood, papillary muscles, or artifacts. B-MORE is calculated as a percent change in mean SI of the end-systolic images at 30 s (vasodilation) compared to 0 s of the breath-hold (vasoconstriction), according to the equation: ΔSI (%) = 100 × [(SI30s − SI0s)/SI0s] [65]. Other markers will be derived from an artificial intelligence analysis of the SI curves across the cardiac cycles during the post-hyperventilation breath-hold.

### ICA with hemodynamic measurements

2.5

The time between ICA and CMR will be a maximum of 6 weeks. ICA is clinically indicated for the study participants. In addition to standard ICA, FFR, iFR, resting Pd/Pa, CFR, and IMR measurements of all main coronary arteries will be performed. All images and invasive measurements will be obtained and interpreted by experienced interventional cardiologists, blinded to the results of CMR. Details on the methodology of ICA and hemodynamic measurements are presented in Supplementary Material.

### Follow-up CMR

2.6

To assess the impact of revascularization on myocardial perfusion and oxygenation, a follow-up CMR scan will be performed 3 months after ICA using the same protocol as the baseline scan to quantify changes in MBF, MBV, and myocardial oxygenation following coronary revascularization. In case of revascularization performed separately more than 1 day following ICA, the follow-up CMR will be performed 3 months after the (last) revascularization procedure.

### Clinical follow-up

2.7

Data on clinical follow-up will be collected at 3, 6 months, 1 and 3 years after ICA (or after the [last] revascularization procedure if performed separately). Data on medical history since study inclusion, including SAQ-7 score, current pharmacotherapy, acute coronary syndromes, elective or emergency revascularization, and hospital admissions for cardiovascular causes, will be collected. Moreover, information on cardiovascular and all-cause death will be collected. If available, upon permission, the data will be collected from the electronic patient records. If electronic patient record will not be available or deemed insufficient, the data will be collected via telephone.

### Definition of outcomes/events

2.8

#### Diagnosis of obstructive CAD and CMD

2.8.1

For the primary endpoint analysis, hemodynamically significant (obstructive) CAD will be diagnosed if the FFR is ≤0.80 or the diameter stenosis is ≥90% (and if FFR was not obtained due to safety reasons) in at least one major coronary artery. Additional analyses will be performed for the FFR cut-off values of ≤0.75 and ≤0.70. For the secondary endpoint analyses, obstructive CAD will be defined as 1) iFR <0.9 or if a diameter stenosis ≥90% in at least one major coronary artery; 2) Pd/Pa ≤0.91 or if a diameter stenosis ≥90% in at least one major coronary artery. CMD will be diagnosed if invasively measured CFR <2.0. Additional analyses will be performed for CMD defined as CFR <2.5 or IMR ≥25. Definitions of other clinical outcomes and events, including cardiovascular death, myocardial infarction, ischemia-driven revascularization, and stroke, are presented in Supplementary Material.

### Statistical considerations

2.9

#### Sample size and power calculation

2.9.1

Sample size and power calculation were performed according to the primary endpoint. Based on the literature, we assumed the prevalence of obstructive CAD, as defined by FFR, in the study population to be 45% [72]. A sample with 74 from the positive group and 90 from the negative group achieves an 80% power to detect a difference of 0.09 between the area under the receiver operating characteristics curve (AUC) under the null hypothesis of 0.81 and an AUC under the alternative hypothesis of 0.9, using a two-sided z-test at a significance level of 0.05. The data are continuous responses [30], [72]. The AUC is computed between false positive rates of 0 and 1. The ratio of the standard deviation of the responses in the negative group to the standard deviation of the responses in the positive group is 1. Moreover, a sample of 75 from the positive group and 92 from the negative group achieves 80% power to detect a difference of 0.09 between a diagnostic test with an AUC of 0.81 and another diagnostic test with an AUC of 0.9 using a two-sided z-test at a significance level of 0.05. The correlation between the two diagnostic tests is assumed to be 0.6 for the positive group and 0.6 for the negative group. The drop-out rate in our study has been assumed 10%, which is comparable to other prospective diagnostic studies on stress-perfusion CMR and our previous experience in performing diagnostic studies on non-invasive imaging techniques (including CMR) in the detection of obstructive CAD [73], [74], [75]. Therefore, incorporation of the 10% drop-out to the sample size described above (74 from the positive group and 90 from the negative group, in total 164) results in a total sample size of 182 patients (which should also be sufficient to detect a significant difference between two diagnostic tests as described above).

#### Statistical analysis

2.9.2

The statistical analysis will be performed using SPSS software package (IBM SPSS Statistics 20.0, Chicago, Illinois) and MedCalc (MedCalc Software 12.7.8.0, Mariakerke, Belgium). For the primary objective of the study, to validate the QP CMR against FFR (similarly for ΔT1 mapping and OS-CMR), first, intraclass correlation coefficients will be calculated, and second, Bland-Altman plots will be constructed. This will be performed for all comparisons between two continuous variables. Moreover, using FFR ≤0.8 as a definition of a hemodynamically significant coronary artery obstruction, AUCs will be determined for prediction of CAD using quantitative measures of QP CMR, ΔT1, and B-MORE, and perfusion defect score for conventional visual assessment of first-pass perfusion stress CMR. AUCs will be compared using the DeLong method. Diagnostic performance measures (sensitivity, specificity, PPV, NPV, and accuracy) will be calculated for the entire cohort, including 95% confidence interval. To prevent overestimation of the sensitivity, specificity, PPV, NPV, and accuracy, a balanced five-fold cross-validation will be performed. Comparison of sensitivity, specificity, and accuracy between different imaging modalities will be performed using McNemar’s test. Results will be considered statistically significant if p-value <0.05.

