- Diagnostic accuracy (sensitivity, specificity, accuracy, AUC, PPV, NPV) of ΔT1 to detect obstructive CAD, as defined by FFR - Diagnostic accuracy (sensitivity, specificity, accuracy, AUC, PPV, NPV) of OS-CMR (B-MORE) to detect obstructive CAD, as defined by FFR - Head-to-head comparison of diagnostic accuracies (sensitivity, specificity, accuracy, AUC, PPV, NPV) of QP CMR (stress MBF, stress rMBF, MPR, rMPR), ΔT1, OS-CMR, and conventional visual assessment of GBCA-based first-pass perfusion imaging to detect obstructive CAD, as defined by FFR - Diagnostic accuracy (sensitivity, specificity, accuracy, AUC, PPV, NPV) of QP CMR (stress MBF, stress rMBF, MPR, and rMPR) to detect obstructive CAD, as defined by iFR and resting Pd/Pa - Diagnostic accuracy (sensitivity, specificity, accuracy, AUC, PPV, NPV) of ΔT1 to detect obstructive CAD, as defined by iFR and resting Pd/Pa - Diagnostic accuracy (sensitivity, specificity, accuracy, AUC, PPV, NPV) of OS-CMR (B-MORE) to detect obstructive CAD, as defined by iFR and resting Pd/Pa - Head-to-head comparison of diagnostic accuracies (sensitivity, specificity, accuracy, AUC, PPV, NPV) of QP CMR (stress MBF, stress rMBF, MPR, rMPR), ΔT1, OS-CMR, and conventional visual assessment of GBCA-based first-pass perfusion imaging to detect obstructive CAD, as defined by iFR and resting Pd/Pa - Relation of stress and rest MBF and rMBF, MPR and rMPR, ΔT1 and OS-CMR markers to SAQ-7 Summary score, SAQ-7 Angina Frequency score, SAQ-7 Physical Limitation score, SAQ-7 Quality of Life score (before and after revascularization), and Rose Dyspnea Scale score - Prognostic value of QP CMR (stress MBF, stress rMBF, MPR, and rMPR), stress T1 mapping reactivity and OS-CMR in predicting occurrence of a 1) composite of cardiovascular death, myocardial infarction, ischemia-driven coronary revascularization or stroke; 2) composite of myocardial infarction or ischemia-driven coronary revascularization; 3) composite of cardiovascular death, stroke or myocardial infarction; 4) myocardial infarction; 5) ischemia-driven coronary revascularization; 6) stroke; 7) death from any cause; 8) cardiovascular death
*Tertiary endpoints*

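### McNemar's test treats each CMR technique's cut-off as fixed; if the cut-offs are optima fitted to the study data, equally accurate techniques will differ in sensitivity or specificity well above the 5% rate, and cross-validation does not cure it

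*Protocol article*

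**What the plan says.** Table 1 of the protocol article lists as a secondary endpoint: "Head-to-head comparison of diagnostic accuracies (sensitivity, specificity, accuracy, AUC, PPV, NPV) of QP CMR (stress MBF, stress rMBF, MPR, rMPR), ΔT1, OS-CMR" and the conventional visual read, against FFR. Section 2.9.2 gives the tests. AUCs are compared by DeLong's method. For the threshold-based measures it says: "Comparison of sensitivity, specificity, and accuracy between different imaging modalities will be performed using" McNemar's test. The criterion is "Results will be considered statistically significant if p-value <0.05".

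The same section adds a balanced five-fold cross-validation to guard against optimistic estimates of the threshold-based measures. Section 2.8.1 gives numeric thresholds for the invasive indices (FFR, iFR, Pd/Pa, CFR, IMR). No section gives one for stress MBF, rMBF, MPR, rMPR, ΔT1 or B-MORE, or says how one will be chosen. Nor does the article say whether McNemar's test uses whole-cohort or cross-validated classifications.

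**The concern.** McNemar's test compares two fixed binary tests in the same patients. Its null distribution allows for patient sampling but not for uncertainty in where each threshold lies. A threshold that maximises an empirical criterion is noisy at this sample size. Two indices with identical ROC curves then end up at different operating points: one looks more sensitive, the other more specific.

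Cross-validation removes optimism, because patients are classified by a threshold they did not help to choose. It leaves the variability of the threshold in place, since the training folds overlap heavily and all carry much the same displacement. The plan's own safeguard therefore does not address this problem.

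At stake are statements such as ΔT1 being less sensitive than quantitative perfusion, in a study presented as the first comprehensive head-to-head comparison of these methods. Such a statement could reflect only where two thresholds happened to fall.

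**Working it through.** **Inputs from Section 2.9.1.** 74 positive and 90 negative patients; AUCs 0.81 and 0.90; SD ratio 1; correlation 0.6 in each group; two-sided 0.05.

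**Assumptions not in the article.** Binormal scores, and the cut-off rule, which is varied below.

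**Reproducing the plan's figure.** The article states no error rate for McNemar's test, so the only figure to reproduce is the power: "A sample with 74 from the positive group and 90 from the negative group achieves an 80% power". The Hanley-McNeil variance is

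V(A) = [A(1−A) + (n₊−1)(A/(2−A) − A²) + (n₋−1)(2A²/(1+A) − A²)] / (n₊n₋)

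- A = 0.81: (0.1539 + 73×0.02457 + 89×0.06887)/6660 = 0.001213, SE₀ = 0.0348.
- A = 0.90: (0.0900 + 73×0.00818 + 89×0.04263)/6660 = 0.000673, SE₁ = 0.0259.
- Power = Φ((0.09 − 1.96×0.0348)/0.0259) = Φ(0.838) = 79.9%.

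This agrees with the stated 80%, so the inputs are read correctly.

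**Simulation.** For each cohort, two scores are drawn with the same AUC (group separation √2·Φ⁻¹(AUC), SD 1) and within-group correlation 0.6. Each score's cut-off is estimated separately in the training folds of a stratified five-fold split and applied to the held-out fold. Exact McNemar tests are then run for sensitivity (positives), specificity (negatives) and accuracy (all). There were 1,500 to 2,000 cohorts per setting; at a true rate of 15%, the Monte Carlo standard error is √(0.15×0.85/1500) = 0.9 percentage points. The techniques are truly equal, so every rejection is false.

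| Cut-off rule | Sensitivity (AUC 0.81 / 0.90) | Specificity (AUC 0.81 / 0.90) | Accuracy |
|---|---|---|---|
| Same fixed cut-off for both | 2.4-3.5% | 2.8-3.8% | 2.9-3.8% |
| Youden | 24% / 15% | 27% / 18% | 7-9% |
| Maximum accuracy | 14-24% | 14-24% | not tabulated |
| Closest to the (0,1) corner | 6.1% / 3.4% | 7.5% / 5.5% | 5.5% / 5.1% |
| Midpoint of group means | 1.5% / 1.8% | 2.2% / 1.8% | 3.6% / 2.4% |
| Fixed 90% sensitivity | 0% / 0% | 23% / 19% | 16% / 11% |

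Fixed cut-off and maximum-accuracy entries are ranges over the settings run. Separate runs gave 15-25% for maximum accuracy and 4-9% for closest-to-corner, hence the rounded ranges of about 15-27% and about 3-9%.

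**Reading the table.**
- The fixed cut-off row holds its level, so the excess comes from estimating the cut-offs, not from the test or the sample size.
- Without cross-validation, Youden gives 34% / 22% for sensitivity and 38% / 25% for specificity. Cross-validation reduces the excess but does not remove it.
- If one technique has a fixed cut-off and the other a cross-validated Youden cut-off, the rates are 15% / 10% for sensitivity and 19% / 12% for specificity.
- The uncorrected chi-square form of McNemar's test gives higher rates: under Youden, 29% / 20% and 33% / 23%.

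**The case against.** The article never says that cut-offs are estimated separately for each technique. A condensed article may leave the selection rule to the full protocol or analysis plan, so its absence is no fault in itself. This stands, and the point must be conditional. What remains is that the article fixes the test and the 0.05 criterion. Cross-validating a single-variable index serves a purpose only if something, in practice the threshold, is fitted to the data.

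A reader might infer that McNemar's test fails for every pair of techniques. The table does not support that: the rate runs from below nominal to about five times nominal (27/5 = 5.4), depending on the rule. Accuracy is only mildly affected under Youden.

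A reader might also quote the chance that at least one of sensitivity and specificity is significant (40% / 28% under cross-validated Youden). That figure mixes in multiplicity: with a fixed cut-off it is already 5.3-6.6%. The per-test rates are the right evidence.

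A reader might further infer that PPV and NPV are to be compared by McNemar's test. Section 2.9.2 confines that test to sensitivity, specificity and accuracy. A method for PPV and NPV may stand in the fuller plan.

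Finally, the comparison is secondary, and the planned DeLong test needs no cut-off. A pure threshold artefact would typically show as opposite shifts in sensitivity and specificity without an AUC difference, which would help expose it. This limits the consequence but does not make the stated p-values valid.

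**Conclusion.** The point holds conditionally. If the cut-offs are empirical optima such as Youden or maximum accuracy, McNemar's test on cross-validated classifications falsely declares a difference in sensitivity or specificity in about 15-27% of studies per test, roughly three to five times the nominal 5%. With closest-to-corner cut-offs the rate is about 3-9%, and with a midpoint-of-means rule it is at or below nominal. Accuracy under Youden is at about 7-9%. A fixed sensitivity target moves the excess to specificity.

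These figures rest on binormal scores, the plan's group sizes, AUCs and correlation, and exact tests. That cut-offs are fitted to the study data is a strong inference from the cross-validation and from the absence of any stated CMR threshold; it is not a statement in the article. The primary endpoint, the sample size and the DeLong comparison are unaffected.

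**What to change.** - Restrict McNemar's test to cut-offs fixed before the FFR data are seen.
- Where cut-offs are estimated from the study data, test differences in sensitivity and specificity with a paired bootstrap that repeats the cut-off selection for both techniques in each resample. State the selection rule in advance.
- Comparing sensitivity at a common, pre-stated specificity is an option. It answers a different question from comparing each technique at its own derived cut-off, so the choice should be deliberate.
- Name DeLong's AUC comparison as the main head-to-head test.

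The cost is analysis wording and a script. No new data are needed, and since patients are still being enrolled the change can be pre-specified. The downside is power: in a limited simulation check the bootstrap rejected in 0-3% of null studies, so it is conservative and fewer pairwise differences will be nominally significant. Its power was not assessed.

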### Data collection and monitoring

2.10

All data collected in the study will be recorded using a dedicated electronic case report form (eCRF). On-site monitoring will be performed by the local Clinical Monitoring Center (CMC, Amsterdam UMC). At the beginning of the study, a full monitoring schedule will be created, and an independent monitor will verify the completeness and quality of eCRF records by comparison with the source data. The number of any missing or uninterpretable diagnostic tests will be recorded. Adverse events are defined as any undesirable experience occurring to a subject during the study, whether or not considered related to study procedures. All adverse events reported spontaneously by the subject or observed by the investigator or the staff will be recorded. The investigator will report all serious adverse events (SAEs) to the accredited medical ethics committee that approved the protocol, except for SAEs that are unrelated to the CMR and/or ICA with FFR, as interpreted by the principle investigator. Due to the minor risk of an adverse event, an independent data safety monitoring board will not be appointed. Reporting of SAEs to the medical ethics committee is thought to be sufficient to monitor the safety of participating subjects.

## Conclusions and implications

3

The ADVOCATE-CMR study is a single-center, observational, prospective, cross-sectional cohort study to validate QP CMR, ∆T1, and OS-CMR imaging against invasive gold standards (FFR, iFR, or resting Pd/Pa) for the detection of obstructive CAD. This is the first study comprehensively assessing and comparing head-to-head the diagnostic performance of a range of contrast- and non-contrast-based CMR imaging methods for the detection of FFR-defined obstructive CAD. Based on our results, we expect to establish a validated, time-efficient, and cost-effective diagnostic workflow available to a wide range of general CMR services performing CMR. Finally, these improvements may enable CMR to become an effective, potentially needle-free, non-invasive gatekeeper for ICA in patients with suspected obstructive CAD and may become an alternative for conventional invasive, radiation-based strategies.

